## Abstract

**Background:**

In mental health care, the number of patients with diverse cultural backgrounds is growing. Nevertheless, evaluated training programs for transcultural competence are missing. Barriers for engaging in transcultural therapy can be identified in patients as well as in therapists. Besides language barriers, clinical psychologists report insecurities, for example, fear of additional expenses when involving a language mediator, ethical concerns such as power imbalances, or fear of lack of knowledge or incorrect handling when working with patients from other cultures. Divergent values and concepts of disease, prejudices, and stereotyping are also among the issues discussed as barriers to optimal psychotherapy care. The planned study aims to empower clinical psychologists to handle both their own as well as patients’ barriers through a web-based training on transcultural competence.

**Methods:**

The training includes 6 modules, which are unlocked weekly. A total of *N* = 174 clinical psychologists are randomly assigned to two groups: the training group (TG) works through the complete training over 6 weeks, which includes a variety of practical exercises and self-reflections. In addition, participants receive weekly written feedback from a trained psychologist. The waitlist control group (WL) completes the training after the end of the waiting period (2 months after the end of the TG’s training). The primary outcome is transcultural competence. Secondary outcomes consist of experiences in treating people from other cultures (number of patients, satisfaction and experience of competence in treatment, etc.). Data will be collected before and after the training as well as 2 and 6 months after the end of the training.

**Discussion:**

This randomized controlled trial tests the efficacy of and satisfaction with a web-based training on transcultural competence for German-speaking clinical psychologists. If validated successfully, the training can represent a time- and place-flexible training opportunity that could be integrated into the continuing education of clinical psychologists in the long term.

**Trial registration:**

DRKS00031105. Registered on 21 February 2023.

**Supplementary Information:**

The online version contains supplementary material available at 10.1186/s13063-023-07878-w.

## Administrative information

Note: the numbers in curly brackets in this protocol refer to SPIRIT checklist item numbers. The order of the items has been modified to group similar items (see http://www.equator-network.org/reporting-guidelines/spirit-2013-statement-defining-standard-protocol-items-for-clinical-trials/).

## Introduction

### Background and rationale {6a}

In clinical psychological practice, we see rising numbers of patients with diverse cultural backgrounds^1^. This includes both patients living in the host country for a long time and refugees and asylum seekers who have only recently arrived in the host country [1, 2]. At the end of 2021, 89.3 million people worldwide were forced to displacement of which 1.3 million were hosted in Germany [3]. More than a quarter of residents in Germany (27.3%) had a migration background in 2021 [2]. Due to the war in Ukraine, the number of Ukrainians in Germany increased almost seven times from February to November 2022 [4]. As a result, society is becoming increasingly diverse and the health care system is facing a broad cultural diversity. It is assumed that the need for therapeutic care among incoming patients with diverse cultural backgrounds is at least as high as in the German population [5]. Studies point to an increased prevalence of mental disorders in the third generation of immigrants [6]. Higher rates of mental disorders are particularly found after forced migration (e.g., due to war or other traumatic experiences) as well as in migrants who have only recently arrived in the host country [7]. Yet patients from other cultures are underrepresented in psychotherapeutic care [8]. Several studies have shown that patients with diverse cultural backgrounds are less likely to utilize psychotherapeutic services [9–12].

Numerous reasons were postulated for this, such as limited communication skills, insufficient information about health care, and shame and fear of stigmatization [10, 13]. Mainly due to the cultural mismatch between patients and clinical psychologists, patients with diverse cultural backgrounds drop out of therapy more frequently than people without a migration background [13, 14] and treatment success is lower [15, 16].

Barriers on patients’ and therapists’ ends as well as institutional barriers can eventually explain why therapy is used less and appears to be less successful for patients with diverse cultural backgrounds [13, 15–17]. Institutional barriers include, for example, the limited availability of language mediators, a lack of funding for interpreting services, and in some countries a general lack or limited funding for psychotherapy [9, 12, 18–20]. On the patient side, language barriers, lack of knowledge about care services, and fear of stigmatization may prevent treatment seeking [21–23]. The fear of stigmatization can be accompanied by social withdrawal and isolation, which further exacerbates mental disorders [19]. On the therapist’s side, insecurities in the contact with patients from other cultures, fears of increased effort (e.g., costs for interpreters), but also stereotyping and prejudices can cause only a few patients from other cultures to actually receive treatment [13, 17, 24].

In addition to the personal suffering, economic (workplace costs, lower productivity, unemployment) and health costs are at stake [25]. The challenges presented can only be addressed through holistic solutions that target all three levels—patients, therapists, and institutional barriers.

At the institutional level, it is necessary to establish multicultural teams, psychologically trained interpreters are available, and information is provided to patients in their native language [15]. Healthcare workers should further be trained in transcultural competence and the hiring of native speakers should be promoted. Also, a reduction of access barriers, for example, through simplified language and fewer administrative barriers, is to be encouraged [13, 26].

At the patient level, potential barriers should be reduced through psychoeducational content by providing easy to understand psychoeducation on mental health and treatment options via different and readily available channels (e.g., online information platforms, local institutions, social workers, social media). Information should consist of what mental symptoms and disorders are, what a psychological treatment consists of, and where and how treatment is possible. Providing such information has been shown effective in reducing fears, uncertainties, and stigmas associated with mental health care [27, 28]. An example of such a low-threshold intervention is the so-called tea garden, an intervention for asylum seekers in which specific mental health knowledge and information on treatment options is provided [29, 30].

On the therapist level, training in transcultural therapy should be encouraged. Even though patients with diverse cultural backgrounds do not need a *different* psychotherapy, methods should be applied in a culturally sensitive way [31]. That is, therapists should be aware of patients’ potentially discrepant understanding of Western psychotherapy and migration-specific and cultural factors should be taken into account in treatment, for example when setting therapy goals, discussing explanatory models, or choosing therapeutic techniques [16, 31, 32]. Training to promote transcultural competence is therefore central to increase the therapeutic success of treatment [31, 33]. Studies showed that culturally adapted psychotherapy resulted in superior outcomes for patients with diverse cultural backgrounds [33].

For the definition of transcultural competence, the study draws on the established definition by Sue et al. [34, 35]. It emphasizes that transcultural competence is built on three pillars: *knowledge* (cognitive aspects), *awareness* of attitudes and beliefs of other cultures (affective aspects), and *skills* (behavioral aspects).

To date, there is a lack of evaluated training programs teaching and thereby increasing transcultural competence in clinical psychologists [17, 36]. This is the case even though guidelines exist that highlight learning objectives and structural and content requirements of such training [37, 38]. One training that builds upon these guidelines was recently investigated and its effectiveness was demonstrated in a pilot study [22]. As expected, the training increased the transcultural competence in clinical psychologists in Germany. In addition to transcultural competence, the therapeutic relationship was further improved. Therefore, the researchers assume that training to promote transcultural competence is not only beneficial for therapies with patients with diverse cultural backgrounds, but also has positive effects on therapies regardless of cultural background.

However, such validated training remains scarce. The COVID-19 pandemic has further restricted access to continuing education [39]. Thus, there is an increasing demand to offer training opportunities that are accessible from any location and are time-flexible, allowing participants to learn at their own pace [39]. A web-based training program could reach a wider target group. Preliminary evidence from the US suggests that a web-based training could increase transcultural competence in a pediatric context via a program consisting of six online modules [40].

For this reason, we designed and implemented an online training to promote transcultural competence among clinical psychologists. The intervention builds on the training program developed by [name] with contents from her book on transcultural psychotherapy [41]. A preliminary version of the program, which was primarily based on a web-based textbook approach, was tested in a pilot trial [42]. In the meantime, the training has been incorporated into an interactive web-based platform in which written information is complemented by image-, audio- and video-guided content. The multisensory learning enables the contents to be memorized more effectively [43]. Each module has a pre-designed structure that can be personalized according to the interest of the participants by displaying or skipping further information as desired.

It is expected that our study will increase transcultural competence in all three areas of transcultural competence [34, 35]: knowledge, skills, and awareness (primary outcomes). In addition, we expect that the training will increase treatment satisfaction and competence experienced when working with patients with diverse cultural backgrounds, as well as the number of patients with diverse cultural backgrounds treated (secondary outcomes). In the long term, the training is intended to be integrated into the continuing education of clinical psychologists.

### Objectives {7}

The research aims to achieve the following objectives:To test the efficacy of an online training to improve transcultural competence (primary outcomes) and the experience in treating patients with diverse cultural backgrounds (secondary outcomes). Transcultural competence is measured through the MCI [44] and the OnTracc-questionnaire [45]. The experience in treating patients with diverse cultural backgrounds is measured through questions asking the number of patients, the satisfaction, and the experience of competence in treatment.To identify possible mediators and moderators at the clinical psychologist’s level (own migration background, multilingualism, volunteering for refugees, and patients with diverse cultural backgrounds) which might influence the efficacy of the training on the primary and secondary outcomes.To foster easily accessible, time- and place-independent, high-quality continuing education for clinical psychologists.

### Trial design {8}

Our study is a two-armed, randomized-controlled trial (RCT) with two parallel groups (training group vs. waitlist control group) of equal size (1:1 ratio at randomization). The study is designed as a superiority trial investigating the efficacy of a 6-week transcultural competence training to improve transcultural competence in clinical psychologists as compared to a waitlist control group. Furthermore, potential mediators and moderators of the training effect will be investigated in the trial.

## Methods: participants, interventions, and outcomes

### Study setting {9}

Licensed clinical psychologists and psychologists in training (for at least one year) from German-speaking countries (Germany, Switzerland, Austria) will be recruited. As the study is web-based, participants will take part in the study online via an electronic device (tablet, PC).

### Eligibility criteria {10}

The following inclusion criteria apply to participants:Licensed as clinical psychologists or ongoing clinical psychology training for at least 1 year in one of the psychotherapy procedures approved by the licensing board in the respective countryCurrently working as clinical psychologists or psychologists in training (to be able to conduct practical exercises)Access to a web-enabled device (PC, laptop) with stable Internet connectionSufficiently good knowledge of German to work with the training materialSufficient time and motivation to work on the training for about 1–2 h per week for 6 weeks6.Besides the inclusion criteria, no exclusion criteria are applicable

### Who will take informed consent? {26a}

Potential trial participants receive detailed written information about the study aims and procedure, the randomization process, the content of the training, and the planned assessments. The study team can be contacted at any time by email or phone for questions and clarifications. Participants must agree to the informed consent form prior to study entry. Only after consenting, participants will be forwarded to the initial study questionnaire.

### Additional consent provisions for collection and use of participant data and biological specimens {26b}

n/a. No biological specimens are collected.

### Interventions

#### Explanation for the choice of comparators {6b}

The comparator will be a waitlist control group. To date, there is no similar training that could have been used as an active comparator. In a pilot study, a third active control group was included, which only did the theoretical part of the exercises, but not the self-reflection exercises (awareness component) [42]. Since the training has now been implemented in an interactive Internet platform, it did not seem reasonable to create a parallel training where only theoretical content would be taught. For this reason, the waitlist control condition seemed the most appropriate.

#### Intervention description {11a}

The entire web-based training was tested in a feasibility study with nine clinical psychology master’s students. In interviews, they provided feedback about the structure, content, usability, comprehensibility, and responsiveness of the platform. Criticism and suggestions for improvement were taken into account and directly implemented.

##### Format

The online training lasts 6 weeks. Every week a new module is unlocked, which is expected to take between 1 and 2 h for the participants to complete. Each module contains between 9 and 10 web pages. Modules can be interrupted at any time and continued later, but it is helpful to divide a module into no more than two blocks per week. It has proven helpful to allow 2–3 days between the completion of one module and the processing of the following module. Research indicates that spacing learning units enhances retention [46]. The training includes a symbol that appears twice per module to remind participants to take a short break.

##### Content

Each module starts with the presentation of the three most important learning objectives for this module and offers an overview of its content. Each of the six modules has a distinct focus: (1) cultural concepts, (2) cultural imprinting, (3) prejudices and discrimination, (4) migration process, (5) transcultural diagnostics, and (6) language and communication (Table 1). Each module ends with a short module summary and some concluding exercises. At the end of the module, a preview of the next module is provided. The contents of the training were built on the textbook by [name] and Kizilhan [41] and a preliminary version of the program was tested in a pilot trial [42]. Various experts in the field of transcultural psychotherapy collaborated on the development of the training.

**Table 1 Tab1:** Content of the different modules

Week	Module name and content
1	**Culture as the salt in the soup—introduction to transcultural psychotherapy** Defining culture, culture as spheres [47], the modern concept of culture: web of significance and hybridity [48], cultural configurations of the self (egocentric, sociocentric, ecocentric, and cosmocentric) [49], the introduction of the term “transcultural competence” with its three components: knowledge, skills and awareness [34], goal setting
2	**The own vs. the other cultures—the meaning of cultural imprinting** Norms and rules in the family of origin, “cultural emancipation” [50], importance of one’s own cultural imprint (what is typically German?), raising awareness for other cultures, individualistic and collectivistic cultures, “culture traps,” universality and diversity [50]
3	**They are all the same!—On the role of prejudice & discrimination** Healthcare conditions of patients with diverse cultural backgrounds in psychotherapy [15], definition and distinction of stereotypes and prejudices, development of prejudices (categorization, stereotyping, judgment) [51], functions of prejudice (orientation, adjustment, enhancement of the collective self-esteem, defense function) [52], influence of stereotypes and prejudices on the therapeutic practice, social categorization on intergroup behavior [53], social identity theory [53], ethnocentrism [54]
4	**Of Leaving and Arriving—The Migration Process & Its Consequences** Migration stages (preparatory stage, act of migration, period of overcompensation, period of decompensation, and transgenerational phenomena) with corresponding stress and resilience factors [55], from the country of origin to German health care, the asylum procedure in Germany [56], challenges as a refugee in health care
5	**Culturally sensitive exploration—What should be considered in transcultural diagnostics?** Cultural case history, cultural concepts of distress [57], disorder-specific and culturally sensitive assessment tools, Cultural Formulation Interview [57], linguistic and cultural equivalence in translations, possible biasing influences on the diagnostic process (halo effect, singularity, culturalization, shame, simulation, etc.) [41]
6	**Understanding and being understood—therapeutic relationship, language & communication** Intercultural communication (power asymmetries, collective experiences, images of others, cultural differences) [58], cultural dimensions (high- and low-context culture) [59], language mediation in therapy (procedure, acquisition, and financing) [60], conclusion

##### Didactics

The content is taught through multisensory learning. Besides written information, images, audios, and videos serve to enhance the knowledge transfer. Practical exercises and short knowledge checks motivate the participants to implement their knowledge in practice.

All six modules address the different transcultural competencies (knowledge, skills, and awareness) equally. In order to target the knowledge component, information is provided on various important topics (e.g., the migration process, the origin and function of stereotypes, different cultural dimensions, etc.). The skills are developed in a practice-oriented manner. For example, working with a language mediator is not only explained in writing, but supplemented by a demonstration video. The awareness component is addressed through numerous self-reflection exercises to continually reflect on one’s own therapeutic practice. For example, in module 2 on cultural imprinting, participants are asked about the norms and rules in their family of origin (communication styles, time management, rituals). In module 4 on the migration process, participants are invited to reflect on their own experiences, possible “culture shocks” and how they have dealt with them. The content is always supplemented by “implications for therapy,” which give concrete indications for use in clinical practice.

For a deeper examination of the content, additional texts and information are offered, which are displayed if needed. Three fictional therapists, based on real individuals, guide participants through the training. Via the fictional characters, examples, possible answers to self-reflection questions and other exercises, and inspiration and motivation for the participants are provided.

After each module, participants receive written feedback from a supervisor about the completed exercises and upcoming questions. The supervisors are at least bachelor-level clinical psychologists and receive regular supervision from an experienced clinical psychologist. The feedback is composed of prefabricated text templates and individualized to the participants’ responses. In the feedback, participants are complimented on their engagement; then, they receive individual feedback on the exercises they have completed. If they have noted specific questions in the module, these are also answered by the supervisor. The supervisor further encourages participants to keep up their active participation. Through sending the feedback, the next module will be unlocked. Participants are accompanied throughout the training and have the opportunity to contact the supervisors.

#### Criteria for discontinuing or modifying allocated interventions {11b}

Due to the non-clinical sample, no criteria have been set to discontinue or modify the training. Participants can stop working with the training at any time, without providing an explanation There are no disadvantages from withdrawal, except that in the case of discontinuation, the participants cannot receive the certificate of attendance (i.e., continuing education credits).

#### Strategies to improve adherence to interventions {11c}

Participants are encouraged to attend the training on a weekly basis. At the end of each module, the program suggests participants to plan a timeframe to complete the next module within a week. An online calendar supports this intention. Adherence is further supported by the feedback of a supervisor, who communicates with the participants at least once a week.

If the module has not been worked on after 5 days, the supervisor sends a reminder to encourage the participant to continue. The participant is also asked if and how the supervisor can support them to continue the training. If the participant still has not continued the training 1 week later, an additional reminder email follows. If neither the training is worked on nor are the emails answered for 3 weeks, the participant receives a last e-mail where he or she is asked whether there is still interest in participation. The e-mail also contains the information that the participation will be deleted if neither there is a reply to the e-mail nor the module is processed within the next 7 days. The participant is then considered to have dropped out of the study.

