### Participant timeline {13}

Via a link, participants can access the detailed description and the inclusion criteria of the study online. After accepting the informed consent, the participants will be forwarded to the pre-training assessment (t0). During the pre-training assessment, the control variables as well as the primary (Multicultural Counseling Inventory and OnTracc) and secondary outcomes are measured. The participants will subsequently be randomized. The TG will directly start with the training. After the training (t1) and 2 (t4) and 6 months later (t5), the assessments are carried out again. The WG will complete a control assessment (t1) after the training group has completed the training. They will also complete the 2-month follow-up assessment (t2). After the 2-month follow-up assessment, they will start the training. After the training (t3) and 2 (t4) and 6 months (t5) later, they will complete the assessments. For the participant timeline, please refer to Fig. 1.

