## Statistical methods

### Statistical methods for primary and secondary outcomes {20a}

Outcomes will be evaluated using intention-to-treat (ITT) analysis. Group differences (group: training group vs. waitlist control group) in primary (transcultural competence; MCI and OnTracc) and secondary outcomes (experiences in treating people from other cultures) will be examined using piecewise linear mixed-effects models with repeated measures (time point: pre, post, follow-up 1). Likely will piecewise linear mixed-effects models be used to examine the longer-term effect of the training (including the four time points: pre, post, follow-up 1, and follow-up 2). The significance level will be set at *p* < .05.

Sociodemographic data will be listed by group condition and for the total group. Group comparisons will be examined at baseline to check for successful randomization. Categorical data are reported as *N* (%), continuous data as mean (SD).

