### Methods in analysis to handle protocol non-adherence and any statistical methods to handle missing data {20c}

The data are analyzed according to the intention-to-treat principles, and data of all individuals randomized in this trial will be entered in our analyses. The handling of missing data is reported in tables and results.

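### The inactivity rule in section {11c} ends study participation, not only training, can act in one arm only during the randomized comparison, and conflicts with the intention-to-treat promise

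*Protocol article*

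**What the plan says.** Section {11c} sets out escalating reminders for a participant who is not working on a module. The last step begins "If neither the training is worked on nor are the emails answered for 3 weeks". A final e-mail then warns that "participation will be deleted if neither there is a reply to the e-mail nor the module is processed within the next 7 days". The consequence is stated for the study, not only for the training: "The participant is then considered to have dropped out of the study".

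Four other places bear on this:

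- Section {11b} says that "no criteria have been set to discontinue or modify the training".
- Section {20a} says "Outcomes will be evaluated using intention-to-treat (ITT) analysis", and bases the group comparison on "repeated measures (time point: pre, post, follow-up 1").
- Section {20c} says that "data of all individuals randomized in this trial will be entered in our analyses".
- Section {13} has the waitlist arm assessed while it waits ("The WG will complete a control assessment (t1) after the training group has completed the training") and again at 2 months (t2). Its own training starts only after that.

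**The concern.** Stopping the training and leaving the study are different events. An intention-to-treat comparison needs outcomes from people who stop the training, because they are part of the effect of being offered it. Section {11c} merges the two events: inactivity plus silence makes someone a study dropout.

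The rule is triggered by behaviour towards the modules, and up to t2 only one arm has modules. A silent waitlist member faces no comparable removal in that period. Follow-up in the training group can therefore be cut short for a reason linked to the intervention and plausibly to motivation. At stake is the primary contrast in transcultural competence, which could be shifted in the training's favour. Outcomes that were never requested cannot be recovered at the analysis stage.

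**Working it through.** **Step 1: whom the rule can reach.** Removal needs two conditions together (no module work and no reply) for 3 weeks, and then again for 7 days after the last e-mail ({11c}). The comparison uses pre, post and follow-up 1 ({20a}). Waitlist members get modules only after t2 ({13}). Within the comparison, only training-group members can meet the conditions. Waitlist members meet the rule later, when the randomized contrast is over.

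**Step 2: what happens to their data.** The pre-training assessment precedes randomization ({13}), so every removed person has baseline data. The text deletes participation and does not say that collected data are erased. No section says that removed people still receive the post or 2-month questionnaire. Read literally, a removed person contributes baseline and nothing after it. That is hard to square with {20c}, and a rule that ends participation for inactivity is hard to square with {11b}.

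**Step 3: what the planned model does with this.** A linear mixed model fitted to the available data assumes that, given what was observed, missing values follow the pattern of the person's own group. For someone with baseline only, that pattern is the course of training-group members who stayed.

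**Step 4: illustration of size.** The document gives no dropout rate, so there is no figure of the plan's own to reproduce.

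Inputs:
- effect in those who keep training: 0.5 SD, the planning value in section {14};
- share q of the training group removed: 10%, 20%, 30% (assumed);
- benefit b in those removed: 0 (assumed);
- training-group size: 174 / 2 = 87 ({14}, with the 1:1 ratio in {8}).

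Formulas:
- all-randomized effect = (1 − q) × 0.5 + q × b;
- effect estimated from those who stayed ≈ 0.5;
- overstatement = q × (0.5 − b).

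| q | Training group with follow-up | All-randomized effect (SD) | Estimated (SD) | Overstatement (SD) |
|---|---|---|---|---|
| 10% | 87 × 0.9 ≈ 78 | 0.9 × 0.5 = 0.45 | about 0.50 | 0.05 |
| 20% | 87 × 0.8 ≈ 70 | 0.8 × 0.5 = 0.40 | about 0.50 | 0.10 |
| 30% | 87 × 0.7 ≈ 61 | 0.7 × 0.5 = 0.35 | about 0.50 | 0.15 |

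**Step 5: how the illustration moves.** The overstatement shrinks as b rises and vanishes at b = 0.5. Only the part due to outcomes that the rule itself prevents can be charged to the rule. If none of the removed people would have answered a questionnaire anyway, the rule adds nothing. If all would have answered, the full amount in the table is due to it.

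**The case against.** The strongest case on the other side has five parts.

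- **The rule is narrower than non-adherence.** This stands. A participant who stops the modules but answers an e-mail is not removed, and {11b} lets people stop at any time at the cost of the certificate only. A reader might infer that the comparison becomes adherent training-group members against the whole waitlist. The text does not support that: the rule catches the silent as well as inactive, and the waitlist can lose members too.
- **A dropout label is not exclusion from analysis.** This stands in part. A reader might infer that the data are erased, but the document does not say so, and baseline values can enter the model. What remains is the end of follow-up after baseline.
- **Follow-up may continue anyway.** Section {18b} describes questionnaire reminders without tying them to module completion, and {20b} plans to relate completed modules to outcome. These make continued assessment possible, but neither says that it applies to someone already counted as out of the study. A reader might also infer that slow training-group members have no post-assessment date. That cannot be established: the waitlist sentence in {13} does not show it, and the schedule figure is not available here.
- **The size rests on assumptions.** This stands. A reader might go further and infer a spurious difference even with no training effect. That argument compares raw retained scores, whereas the planned model includes the pre measurement, which takes up the part of the selection that runs through baseline.
- **The analysis plan or a fuller protocol may cover it.** For missing-data methods, yes. For this rule, no: it governs whether outcomes are collected, and {31c} describes the article as the complete protocol.

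**Conclusion.** The point holds in a limited form and should be fixed. As written, section {11c} ends study participation for inactive and silent training-group members, has no counterpart in the waitlist arm before t2, and does not agree with {11b}, {20a} or {20c}. The likely direction of bias is towards the training.

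Its size cannot be determined from the document. The 0.05–0.15 SD overstatement assumes 10–30% removal, no benefit in those removed, and that all of them would otherwise have answered. It is an upper-end case in the last two respects, since some would have gained something from the modules they completed and some would not have answered any questionnaire. The conflict between the sections does not depend on these numbers.

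**What to change.** - Reword {11c} so that inactivity and non-reply close access to the training only, and state that data already collected are kept.
- State in {13} that the post and 2-month questionnaires, with the reminders in {18b}, go to every randomized person in both arms on the same schedule counted from randomization. This applies whether or not the modules are finished, unless the person explicitly withdraws from the study.
- Reconcile {11b}, {11c}, {13} and {20c}, so that stopping the training and leaving the study are defined separately.

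A sensitivity analysis for missing training-group outcomes is optional and can be left to the statistical analysis plan.

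The cost is a wording change, a few more e-mails and possibly a smaller estimated effect. No extra participants are needed. If the sponsor regards the change as an important modification, it goes through the ethics route in {25}.
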